To protect against depressive relapse after the acute phase of depression several psychotherapeutic treatment strategies have evolved [18]. This way alternatives for patients not wanting to maintain antidepressants seem available. Mindfulness Based Cognitive Therapy (MBCT) is one of these approaches of relapse prevention, it is an innovative psychological approach for relapse/recurrence prevention in recurrent depression developed by Segal, Williams & Teasdale [19]. It is an 8-week group-based treatment that integrates elements from mindfulness-based stress reduction (MBSR) [20] and cognitive–behavioural therapy (CBT) [21]. A recent meta-analysis showed that MBCT appears efficacious as a treatment for relapse prevention for those with recurrent depression. MBCT reduces the risk of depressive relapse/recurrence compared with the current mainstay approach, maintenance antidepressants [22]. As MBCT appears to be a viable alternative to antidepressant medication it is possible that mindfulness could provide patients support in the de-identification of thoughts and allowing of uncomfortable physical and mental symptoms, and also help them to deal with possible withdrawal effects.

There is some evidence that MBCT might be useful in supporting tapering of antidepressant medication. Two randomized controlled trials in the UK, offering recurrently depressed patients MBCT with additional tapering support, show successful tapering of Antidepressant Medication (ADM) in 75% [23] and 71% of participants [24]. However, results from a study conducted in the Netherlands were less promising. Only 53% of the patients allocated to the group who received MBCT and tapering support succeeded in tapering their antidepressants [25]. Remarkably, there was a relatively large number of “cross-overs” in this trial, as 12% of patients who were asked to continue their medication after MBCT actually discontinued their antidepressant medication successfully. This latter trial showed that tapering was not necessarily easy even after MBCT, but that the perspective of the patient (e.g. preferences, motives, previous experiences with withdrawal) may have played a significant role. The authors suggested that MBCT for tapering ADM might need to be offered in homogeneous groups of patients who are eager to withdraw from their medication and that it should be specifically tailored to address effects of discontinuation within the mindfulness framework.

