### Sample size

Based upon earlier research we expect a discontinuation rate for patients in the SPD condition of 15% and a 40% discontinuation rate for patients in the SPD + MBCT condition. We used data from Eveleigh [17] to predict discontinuation in the SPD condition (where 6% successful discontinuation was observed according to very strict criteria, and we made adaptations to align with the context of the current setting, e.g. all patients had a clear intention to taper). To estimate the rate in the SPD + MBCT condition, we looked at studies with available data on adherence to tapering after MBCT, ranging between 53 and 71% [23–25]. Again we made a conservative adaptation of 40% to account for differences in time frame (6 versus 15 months), intention-to-treat versus per-protocol sample, and considering the difficulties in discontinuation and withdrawal symptoms as mentioned in the literature [16]. The following assumptions were used in the sample size calculation: power 80%, alpha of 5% and two tailed testing. Due to the fact that the trial will be cluster randomized, the calculated number of patients assuming individual randomization, has to be inflated by a design factor. To account for this an intra-class correlation (ICC) of 0.05 was used, which is commonly used for research including outcome measures [26]. With regard to the mentioned research we also assume a dropout rate of 15%. Taking these figures into account a total of 24 GPs have to be included, with 138 patients participating in the study; including 69 patients per described condition; presenting an estimate of 5 participating patients per GP.

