### Procedure

Eligible GPs will be informed about the study and requested to participate. GP’s will be randomly allocated to either SPD alone or SPD + MBCT. The GPs are asked to identify patients using antidepressant medication for more than 9 months in their electronic prescription system. Between 2016 and 2018 interested GP’s will invite their long-term-users of ADM to discuss tapering via a letter and return form. GPs are requested to inform the research team about the number of patients who will not get an invitation including the reason(s).Patients’ reply forms will be collected by the research team and interested patients will be invited to complete the online screening questionnaire which includes demographic characteristics, ADM-use, the Patient Health Questionnaire [27] and Generalized Anxiety Disorder [28]. Subsequently, they will receive an information brochure about tapering, a decision aid and an invitation to make an appointment with their GP. Patient and GP are encouraged to use the decision aid as a conversation guideline to make a shared decision on whether or not to discontinue the antidepressant medication. After having consulted their GP about tapering and if they decide to start tapering, patients will receive an invitation to participate in the RCT and an invitation for a research interview. During the interview written informed consent that has been approved by the Medical Ethics Committee of Arnhem-Nijmegen will be obtained. The psychiatric structured diagnostic interview that will be conducted [29] will take about 60–90 min altogether. Patients will also be requested to complete baseline measures online. Thereafter patients will be advised to plan meetings with the Mental Health Assistant for their SPD. Those patients allocated to SPD + MBCT will be invited to participate in the first upcoming MBCT course. Follow up measurements take place six, nine and 12 months after baseline using telephone interviews and online questionnaires. The first assessment took place in February 2017, the last assessment will take place in July 2019.

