### Randomization and statistical analysis

To prevent a crossover effect between the interventions, cluster-randomization will be performed with the GP as the unit of clustering. A senior academic statistician will produce the randomization schedule based on a stratified block randomization. Stratification variables consist of region (north, central and east Netherlands) and type of practice (single versus group practice). This schedule will be send in a protected Excel-sheet to a research assistant who will allocate the GP in order of their entry to either intervention or control group. The research assistant will communicate the allocation to the researcher who will, in turn, communicate this to the GP. We are not able to keep the SCID interviewer blind to the patient’s condition. The clinical outcome data will be analysed and reported according to the CONSORT guidelines, i.e. both on an intention-to-treat and per protocol basis. With regard to missing data, sensitivity analyses will be conducted with different types of imputation. Multilevel analyses will be used to account for the hierarchical structure of the data (i.e. multiple assessments nested within patients, patients nested within GPs, and GPs nested within practices).

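### MBCT is given in group courses in one arm only, but the course is missing from the multilevel models and the design factor; if outcomes correlate within courses, precision and power are overstated

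*Protocol article*

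**What the plan says.** **Delivery.** The Background describes MBCT thus: "It is an 8-week group-based treatment". The Interventions section confirms that it is given in group sessions in this trial, by several teachers. Under Procedure, patients in the SPD + MBCT arm are "invited to participate in the first upcoming MBCT course". The SPD arm has no courses.

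**Model.** Randomization and statistical analysis says that multilevel analyses will account for the hierarchical structure. It spells that structure out after an "i.e." as "multiple assessments nested within patients, patients nested within GPs, and GPs nested within practices". Neither course nor teacher appears.

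**Sample size.** The number for individual randomization "has to be inflated by a design factor", for which "an intra-class correlation (ICC) of 0.05 was used" with an estimated 5 patients per GP. The remaining inputs are "power 80%, alpha of 5% and two tailed testing", rates of 15% and 40%, and 15% dropout. The result is 24 GPs and 138 patients, 69 per arm. No allowance is made for clustering by course.

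**The concern.** Patients in one course share a teacher, a group and a calendar period, so their outcomes may be more alike than those of patients in different courses. Entry to a course follows timing rather than GP, so this dependence is not nested in GP or practice. It also exists in one arm only. A model with GP and practice terms then has no component that represents it fully, and some of the between-course variance is treated as independent patient-level noise.

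The error favours finding an effect: intervals for the treatment difference are too narrow and the test rejects too often. The sample size has the same gap, so the stated power holds only if outcomes do not correlate within courses. This is more than detail left to an analysis plan, because the article itself fixes the list of levels and the design factor.

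**Working it through.** **1. Reproduce 138.** The inputs are those of the Sample size section, and p̄ = (0.15 + 0.40)/2 = 0.275.

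- Per arm, individual randomization: n = [1.96·√(2·0.275·0.725) + 0.8416·√(0.15·0.85 + 0.40·0.60)]² / 0.25² = 48.9, rounded up to 49.
- GP design factor: 1 + (5 − 1)·0.05 = 1.20.
- With 15% dropout: 49·1.20/0.85 = 69.18, i.e. 69 per arm and 138 in total, as stated.
- Power check with 69·0.85 = 58.65 evaluable per arm: SE under the null = √(0.275·0.725·2.40/58.65) = 0.0903. SE under the alternative = √((0.1275 + 0.24)·1.20/58.65) = 0.0867. Power = Φ((0.25 − 1.96·0.0903)/0.0867) = 80.0%.

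GP clustering and dropout use up the whole inflation, so nothing is left for the course.

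**2. Add the course in one arm.** Let g be patients per course and ρ the course ICC. **Neither is in the article; both are assumed here.** The SPD + MBCT design factor becomes D = 1.20 + (g − 1)·ρ, and SPD stays at 1.20. For g = 10 and ρ = 0.05, D = 1.20 + 9·0.05 = 1.65.

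**3. Type I error of the planned model (no course term).** True to assumed variance under the null is (1.20 + D)/2.40. For D = 1.65 this is 2.85/2.40 = 1.1875, so the true SE is 1.090 times the model SE. Type I error = 2·[1 − Φ(1.96/1.090)] = 7.2%.

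**4. Power of a model that allows for the course.** SE under the null = √(p̄(1 − p̄)(1.20 + D)/58.65). SE under the alternative = √((0.1275·1.20 + 0.24·D)/58.65). For D = 1.65 the latter is 0.0968. With p̄ = 0.275 the former is 0.0984 and power is 72.2%. With p̄ weighted by effective sample size (0.255) it is 0.0961 and power is 73.8%. The power ranges below reflect only this choice of pooling.

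| Course ICC (assumed) | Patients per course (assumed) | Type I error, planned model | Power, model with course |
|---|---|---|---|
| 0.01 | 8 | 5.3% | 79% |
| 0.01 | 12 | 5.5% | 78% |
| 0.05 | 8 | 6.7% | 74–75% |
| 0.05 | 10 | 7.2% | 72–74% |
| 0.05 | 12 | 7.7% | 71–73% |
| 0.10 | 8 | 8.5% | 68–71% |
| 0.10 | 12 | 10.5% | 63–67% |

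The last two columns describe different analyses. If the planned model keeps its uncorrected critical value, it rejects with probability Φ((0.25 − 1.96·0.0903)/0.0968) = 77.5% at g = 10, ρ = 0.05, but at a true size of 7.2%.

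**5. How far the GP level absorbs the course.** A simulation used 12 GPs of 5 patients per arm and a GP-level t-test that ignores the course, with 4,000 runs per setting (Monte Carlo SE about 0.35 points).

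- Course ICC 0.05: type I error was 6.1% (8 per course) and 7.8% (12 per course) when courses mixed GPs, against 5.7% and 7.3% when courses were filled in GP order.
- Course ICC 0.10: 7.7% and 10.2% mixed, against 6.8% and 8.3% in GP order.
- Course ICC 0: 4.7% to 5.8% over all settings.

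**The case against.** The case against has several parts, and most of it limits the size of the point.

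- **The effect is conditional.** The article gives no course ICC, course size or number of courses. At a course ICC of 0.01 the loss is 1 to 2 points of power and at most half a point of type I error. A reader might infer that the standard error is certainly too small. The documents support this only if outcomes correlate within courses.
- **The GP term is not useless.** GPs are spread over three regions and invite their own patients, so one GP's patients may share a course. The GP term then absorbs part of the variance, as step 5 shows. A reader might infer that the GP and practice terms capture none of it, but the article does not say how courses are composed. Patients who attend no course carry no course effect.
- **Not every outcome is affected through this list.** A reader might infer that all secondary outcomes share the fault. The quoted levels govern the multilevel models. Time to relapse or recurrence is planned as Cox regression, and costs use cluster-robust standard errors.
- **Inflated error and the lower power are not two properties of one analysis.** The first belongs to the planned model, the second to the corrected one.
- **The course variance will be poorly estimated.** With 69 patients and 8 to 12 per course there are only about 6 to 9 courses, so a zero estimate is quite possible. This argues against a rule that drops the term when its variance is estimated at zero, since that would make the model depend on the data and could bring back the under-coverage.
- **Restating power cannot change recruitment.** The last assessment was due in July 2019, the month of publication.

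All of this stands as qualification. None of it supplies the missing level or reverses the direction of the error.

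**Conclusion.** The point holds in conditional form. The article creates group clustering in one arm, lets it cut across GPs, and omits it from both the listed model levels and the design factor. For any positive course ICC that the GP and practice terms do not absorb, the primary and multilevel secondary analyses are anti-conservative. The sample size has no slack to cover it.

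The size rests on assumed inputs. It is negligible near a course ICC of 0.01. It is material at 0.05, the value the article itself uses for GPs, where type I error is about 7% and a model with the course has about 72–74% power at 10 per course. It is serious at 0.10 with 12 per course, at about 10% and 63–67%. The type I figures are towards the upper end, because they give the GP term no credit for patients of one GP who share a course. No single corrected power figure can be read from the documents.

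**What to change.** - **Data.** Record the MBCT course each patient attends. The article does not say whether this is already done.
- **Analysis.** Fit the primary and the multilevel secondary models with a course random effect that applies in the SPD + MBCT arm only (partially nested, cross-classified with GP; SPD patients carry none). At the least, make this a prespecified sensitivity analysis, reported beside the GP-only model whatever course variance is estimated.
- **Power statement.** Say that the 80% assumes no clustering by course, and give the range under stated course sizes and course ICCs instead of one replacement figure.

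The cost is analysis-plan wording and one identifier per patient, with no change to design, recruitment or care. The downsides are slightly wider intervals, a less favourable power statement, and an imprecise course variance because there are few courses.

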### Primary analysis

The primary analysis is aimed at comparing the effects of SPD and SPD + MBCT with regard to the proportion of patients who fully discontinue their antidepressant medication within 6 months. Full discontinuation is defined as using 0 mg antidepressant medication before or at the 6-month assessment. Patients who drop out before this assessment will be classified as ‘not able to discontinue’ (for the primary outcome variable). However sensitivity analyses will be conducted to examine different types of imputation. We will use a multilevel logistic regression model for repeated measures to analyze differences between the two conditions on baseline, 6 months, 9 months and 12 months follow-up measurements.

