#### Primary outcome measure

Our primary outcome will be full discontinuation of antidepressant medication (= 0 mg) within 6 months after starting the intervention. Use of medication will be measured with daily calendars. Patients will be invited to fill out paper calendars describing their type of antidepressant, daily milligrams used and consultations to GP or mental health assistant regarding tapering. In case of missing data in the reports, the GP will be contacted to check the GP prescription database. This latter solution is considered reliable as in the Netherlands all patients are linked to only one GP who collects all medical information for a particular patient.

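### The primary outcome rule for dropouts conflicts with the success definition and with the GP record look-up, so known or retrievable successes can be coded as failures

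*Protocol article*

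**What the plan says.** Three sections of the protocol article bear on patients who drop out.

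- **Primary analysis.** Success is 0 mg of antidepressant at or before the 6-month assessment. The next sentence reads "Patients who drop out before this assessment will be classified as" not having managed to discontinue. Sensitivity analyses with other types of imputation are planned.
- **Primary outcome measure.** Medication use comes from daily calendars. "In case of missing data in the reports, the GP will be contacted to check the GP prescription database". The section calls this source reliable, because each Dutch patient is linked to a single GP who holds all medical information.
- **Sample size.** "we expect a discontinuation rate for patients in the SPD condition of 15% and a 40% discontinuation rate for patients in the SPD + MBCT condition". The 40% was lowered from published figures partly "to account for differences in time frame (6 versus 15 months), intention-to-treat versus per-protocol sample". The other inputs are "power 80%, alpha of 5% and two tailed testing", an ICC of 0.05 and 15% dropout. The result is 24 GPs and 138 patients, 69 per arm, "presenting an estimate of 5 participating patients per GP".

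**The concern.** The success definition looks at anything recorded up to month 6. The dropout rule looks only at whether the patient was still in follow-up at month 6. They give different answers for a patient who reached 0 mg and then left, and the text does not say which prevails.

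Dropping out is also an obvious reason for calendar data to be missing, so the GP look-up and the failure rule can both apply to the same patient. One retrieves the outcome, the other imputes it. Two analysts following the article could code the same patient differently in the primary analysis of a trial in which patients, GPs and the research team know the allocation.

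Applied as written, the failure rule replaces outcomes that are known, or could be known, with failure. That pulls the two rates together, and if dropout differs by arm it biases the comparison. The sensitivity analyses would show how much the result depends on the rule, but they do not change the primary coding.

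**Working it through.** **The rules side by side**

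| Patient | Success definition | GP look-up | Dropout rule |
|---|---|---|---|
| 0 mg on calendar in month 4, leaves in month 5 | success | not needed | failure |
| Leaves in month 3, GP record shows 0 mg before month 6 | success | success | failure |
| Leaves in month 3, no usable GP record | unknown | unknown | failure |

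Only the third row is free of conflict.

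**How many patients**

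15% of 138 = 20.7, so up to about 21 patients (10.35 per arm). If they would have discontinued at the planned rates, the successes among them number 10.35 x 0.15 + 10.35 x 0.40 = 1.6 + 4.1, or about 6.

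**Effect on the comparison, equal dropout**

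Assume 15% and 40% apply to patients with data and to dropouts alike, dropout is 15% in each arm, and every dropout is coded as failure.

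- SPD: 0.15 x 0.85 = 12.75%. SPD + MBCT: 0.40 x 0.85 = 34%.
- Risk difference: 25 points becomes 21.25 points.
- Odds ratio, the scale of the planned logistic model: (0.40/0.60)/(0.15/0.85) = 3.78 becomes (0.34/0.66)/(0.1275/0.8725) = 3.53.
- Risk ratio: 40/15 = 34/12.75 = 2.67, unchanged.

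**Unequal dropout (illustration only; the article gives no dropout by arm)**

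- 10% in SPD, 20% in SPD + MBCT: 13.5% versus 32%, odds ratio 3.02.
- 20% in SPD, 10% in SPD + MBCT: 12% versus 36%, odds ratio 4.13.

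The first understates 3.78 and the second overstates it.

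**The plan's sample size**

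- Pooled two-proportion formula, 15% versus 40%, two-sided 5%, 80% power: n = [1.96 x sqrt(2 x 0.275 x 0.725) + 0.842 x sqrt(0.15 x 0.85 + 0.40 x 0.60)]^2 / 0.25^2 = 48.9, so 49 per arm.
- Design effect with 5 per GP: 1 + 4 x 0.05 = 1.20, and 49 x 1.20 = 58.8 per arm. 58.8/5 = 11.8, so 12 GPs per arm.
- Dropout: 58.8/0.85 = 69.2, so 69 per arm and 138 in total.

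The stated figures reproduce, with 80.0% power on 69 x 0.85 = 58.65 patients with data per arm. The division by 0.85 treats dropouts as leaving the analysis, whereas the dropout rule keeps them in it.

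**Power with all 69 per arm analysed and every dropout a failure (15% in each arm)**

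| Meaning of 15% and 40% | Rates analysed | Design effect 1.20 | Design effect 1.2375 |
|---|---|---|---|
| Rates among patients with data | 12.75% vs 34% | 77.5% | 76.2% |
| Intention-to-treat rates | 15% vs 40% | 86.1% | 85.0% |

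The second design effect is 1 + 4.75 x 0.05, from 138/24 = 5.75 enrolled patients per GP. The stated 5 per GP fits patients with data: 138 x 0.85 = 117.3, and 117.3/24 = 4.9.

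**The case against.** The look-up can be read as filling calendar gaps for patients still in follow-up, and the failure rule as covering those who have left. On that reading the two do not collide. Counting dropouts as failures is also a recognised conservative convention, and sensitivity analyses with other imputations are already planned.

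Part of this stands. The text does not say that one rule overrides the other, so it is too much to say that successes will certainly be miscoded. But the look-up carries no restriction to patients still in follow-up, and separating the scopes does not remove the conflict inside the Primary analysis section for someone already recorded at 0 mg.

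The attenuation is also modest: the risk ratio does not move under equal dropout, and the odds ratio moves only from 3.78 to 3.53. If dropouts in truth discontinue less often than others, failure coding is nearer the truth and the distortion is smaller.

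A reader might infer more than the article supports:

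- **That the sample size adds a third incompatible dropout rule.** The 15% there is a planning allowance, not a rule for coding outcomes.
- **That the trial is underpowered.** The 40% was lowered partly for intention-to-treat, so dropouts may already be inside it. Power would then be 85% to 86%. If only the 40% is an intention-to-treat rate (12.75% versus 40%), it is 92.3% with design effect 1.20.
- **That dropout will be higher with MBCT.** The burden of the course bears on attendance. The article does not equate missing sessions with leaving before the 6-month assessment.
- **That recruitment would stop at 24 x 5 = 120.** The article fixes 138 and calls 5 per GP an estimate.

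**Conclusion.** The point holds for the coding of the primary outcome. The Primary analysis section contradicts itself for patients who reach 0 mg and then leave, and it conflicts with the Primary outcome measure section for dropouts whose use the GP record could show. No order is given.

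Up to about 21 of 138 patients fall under the failure rule at the planned dropout. If they would have discontinued at the planned rates, about 6 successes would be coded as failures, and the expected difference would shrink from 25 to about 21 points. With unequal dropout, which is an assumption here, the bias can go either way.

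The sample size is correct on its own inputs. What it lacks is a statement of whether 15% and 40% already count dropouts as failures. Without it, power at 138 under the failure rule lies at about 76% to 77.5% on one reading and 85% to 86% on the other. A power loss is therefore not established.

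**What to change.** State one order for the primary outcome:

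1. Classify every enrolled patient, including those who stop follow-up, from the calendar.
2. Where the calendar does not settle the outcome, use the GP prescription record.
3. Count failure only when neither source has data.

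Keep all-dropouts-as-failure and multiple imputation as sensitivity analyses.

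In the Sample size section, state whether 15% and 40% are intention-to-treat rates or rates among patients with data, and say that 5 per GP refers to patients with data while 5.75 are enrolled. If power is restated, it should be for the rule adopted. Even if 15% and 40% are rates among patients with data, retrieving 25%, 50% or 75% of dropouts from the GP at the same rates gives 79.9%, 82.1% or 84.2% (design effect 1.20).

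The cost is a few sentences and record look-ups for about 20 patients, using a procedure that is already planned.

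### The primary aim is a 6-month proportion, but the named repeated-measures multilevel logistic model gives a patient-conditional odds ratio whose size depends on behaviour after month 6

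*Protocol article*

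**What the plan says.** Under Primary analysis, the Protocol article compares the two arms "with regard to the proportion of patients who fully discontinue their antidepressant medication within 6 months". The endpoint is met by reaching 0 mg at or before the 6-month assessment, and patients who drop out earlier count as failures, so each patient contributes one yes/no value. The same section then names the method: "We will use a multilevel logistic regression model for repeated measures to analyze differences between the two conditions", applied to baseline and the 6-, 9- and 12-month follow-ups. Randomization and statistical analysis gives the levels: "multiple assessments nested within patients, patients nested within GPs, and GPs nested within practices".

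Sample size is planned on proportions: "we expect a discontinuation rate for patients in the SPD condition of 15"% and "a 40% discontinuation rate for patients in the SPD + MBCT condition".

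The article names no effect measure (risk difference, risk ratio or odds ratio) and no step from the model back to proportions. Safety and monitoring lets patients restart medication at any time, but no restart rate or between-patient variance is given.

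**The concern.** A logistic model with a patient level has a patient random effect. Its arm coefficient compares the odds of being off medication for two patients with the same value of that effect, one in each arm. It does not compare the proportions off medication in the two arms. The two scales separate as the between-patient variance grows, and that variance is estimated from how consistent each patient is across the repeated assessments. Whether someone takes an antidepressant is likely to be correlated from one visit to the next, so the gap could be wide.

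At stake is the meaning of the headline result. Two trials with identical 6-month proportions could report very different odds ratios solely because their patients restarted, or stopped late, at different rates between months 6 and 12. The primary endpoint does not measure that period. Such an odds ratio also cannot be set against the 15% and 40% on which the trial was planned.

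**Working it through.** **Inputs from the article (Sample size).** Proportions 15% and 40%; "power 80%, alpha of 5% and two tailed testing"; "an intra-class correlation (ICC) of 0.05 was used"; "we also assume a dropout rate of 15"%; 5 patients per GP.

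**1. Reproduce the plan's own figure.** Two-proportion formula with pooled variance under the null and no continuity correction:

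n = [1.960 × √(2 × 0.275 × 0.725) + 0.842 × √(0.15 × 0.85 + 0.40 × 0.60)]² / 0.25² = 48.88 per arm.

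Design effect: 1 + (5 − 1) × 0.05 = 1.2. Dropout: divide by 0.85. Result: 48.88 × 1.2 / 0.85 = 69.0 per arm, 138 in total. This matches the article, so the trial is sized on a contrast of population proportions.

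**2. That contrast on the usual scales.** Difference 25 points; risk ratio 0.40/0.15 = 2.67; marginal odds ratio (0.40/0.60)/(0.15/0.85) = 3.78.

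**3. Conditional odds ratio for the same proportions.** For a normal random intercept with SD s on the logit scale, find the two intercepts a and b for which the average of expit(a + s·z) over a standard normal z is 0.15 and the average of expit(b + s·z) is 0.40. The conditional odds ratio is exp(b − a). The latent ICC is s²/(s² + π²/3). The values of s are assumptions.

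| Random-intercept SD | Latent ICC | Conditional odds ratio |
|---|---|---|
| 0 | 0 | 3.78 |
| 1 | 0.23 | 4.75 |
| 2 | 0.55 | 8.0 |
| 2.77 | 0.70 | 13.1 |
| 5.44 | 0.90 | 89 |
| 7.5 | 0.945 | 420 |

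For example, at s = 2 the intercepts are −2.752 and −0.668, and exp(2.084) = 8.0.

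**4. Link to behaviour after month 6.** Month-6 proportions were fixed at exactly 15% and 40%. From month 6 to 9 and from 9 to 12, patients moved off and on medication at assumed rates, equal in both arms. A random-intercept logistic model with time by arm was fitted by maximum likelihood to the expected data at months 6, 9 and 12.

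| Restart per 3 months | New stops per 3 months | Fitted patient SD | Conditional odds ratio at month 6 | Month-6 proportions after averaging over the random effect |
|---|---|---|---|---|
| 30% | 15% | 2.5 | 11 | 0.150, 0.400 |
| 30% | 10% | 3.1 | 16 | 0.150, 0.400 |
| 20% | 10% | 4.0 | 30 | 0.151, 0.400 |
| 20% | 5% | 5.4 | 87 | 0.151, 0.400 |
| 10% | 5% | 8.0 | 578 | 0.151, 0.400 |

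The last odds ratio is unstable. A separate simulation of the same rates gave about 460, and a version with the proportions kept constant over time and 10% restarting gave about 1,200.

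**5. GP effect only, one 6-month value per patient.** An ICC of 0.05 read on the latent scale is a GP SD of 0.42 and gives 3.94. Read on the proportion scale at 27.5%, it is an SD of 0.52 and gives 4.04. Both are close to 3.78, so GP clustering contributes little; the patient level causes the gap.

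**The case against.** The strongest reply is that the article states an aim and a class of model and never says that the patient-level odds ratio will be the reported effect. Which summary to extract is often left to an analysis plan, which may exist but is not shown. This stands in part: the article does not commit to the odds ratio, and it speaks of a proportion, not of a difference in proportions. But it does fix the model for a once-per-patient endpoint, and that model, followed as written, returns an odds ratio that reflects persistence after month 6.

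A reader might infer that the model makes the 15% and 40% unrecoverable. It does not: averaging over the random effect returned them to within 0.1 point in every fit. They are lost only if the odds ratio is given alone.

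A reader might also infer that the test is invalid or that the effect is exaggerated. Neither follows. A conditional odds ratio of 1 goes with equal proportions, and 3.8 and 30 can be the same effect on two scales. No bias, type I error inflation or loss of power has been shown.

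Finally, it is tempting to assert that status hardly changes and that an odds ratio in the hundreds is to be expected. The article does not support this: it allows restarting and makes a lower restart rate a secondary hypothesis. Odds ratios of 11 to 16 already assume 30% restarting every 3 months, which is not rare change. The fits also leave out the baseline row and the GP and practice levels and use large-sample data, so they show direction and order of size and do not forecast the trial's result.

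**Conclusion.** The concern holds as a mismatch between the stated target and the scale of the stated model's arm coefficient. For identical 6-month proportions of 15% and 40%, the conditional odds ratio ran from 11 to several hundred across the restart and late-stop rates examined, and from about 5 to 8 under moderate between-patient SDs of 1 to 2. The comparison values are 3.8 marginally and about 4 with a GP effect alone. The spread rests entirely on assumed persistence, and the top of the range is too unstable to quote as a figure. The consequence is for estimation and interpretation: the conditional odds ratio is unsuitable as the primary effect size. This should be corrected before analysis, but it does not threaten the validity of the comparison.

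**What to change.** State that the primary effect is the difference between arms in the proportion fully discontinued within 6 months, with the risk ratio alongside and a 95% CI that allows for GP clustering. Either of two routes will do: a model of the single 6-month outcome with a GP effect, converted to proportions, or the multilevel model already named, standardised by averaging predicted probabilities over the random effects and all randomised patients. Report the 9- and 12-month contrasts as standardised proportions too. If the patient-conditional odds ratio is shown, label it as such and do not present it as the effect size.

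The cost is a sentence or two in the analysis section and a small extra computing step. No new data and no design change are needed, and the sample size stays as it is because it already rests on proportions.
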